### Study intervention

#### Baclofen intervention

Clinical trials on baclofen for alcohol dependence treatment have used baclofen at a dose of 30 mg ⁄d [29-31] over 30 to 120 days. This is within the low therapeutic range for muscle spasms. However, Garbutt and colleague’s [32] suggested that 30 mg of baclofen per day may be an insufficient dose for some patients to achieve abstinence. Additionally, baclofen effectiveness for GHB dependence could be smaller, since tolerance may occur due to recent abuse of GHB and a possible substitution function (as treatment will be started immediately after detoxification).

Based on these results and the unpublished results of a small dose finding experimental treatment study in our treatment center, where patients reported limited effect of baclofen 30 mg per day, we decided to administrate a dose of 45 mg to a maximal dose of 60 mg per day orally to avoid the risk of (co) intoxication. In this study baclofen will be administrated orally three times daily as usually recommended [22] and started with a total dose of 15 mg per day. During the first 10 days baclofen will be gradually increased with 15 mg per day every 3 days up to the chosen minimum dose of 45 mg, or a maximum dose of 60 mg in case no effect is reported at 45 mg after 2 weeks. This dose will subsequently be maintained for a period of 10 weeks. Successively, baclofen will be tapered off to 0 mg in 2 weeks (see Table 1). Patients will be asked to avoid abrupt termination of baclofen and will be guided by their physician to avoid complications of baclofen withdrawal. Patients who wished to continue the baclofen treatment will be offered an outpatient counselling and medication by their physician for another 3 months.

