The EuroQol-5D (EQ-5D) will be used to measure changes in patients’ health-related quality of life. For the overall quantification of health status as a single index we will use the standard EQ-5D classification system developed by the EuroQol Group [40]. The EQ-5D is a widely used multi-attribute system available to determine health state preferences (utilities). It is a simple self-report instrument which assesses 5 domains of general health and functioning: mobility, self-care, usual activities, pain/discomfort and anxiety/depression. This is along a 3-point scale (1 = no problems, 2 = some problems and 3 = extreme problems). Based on the descriptive classification of the EQ-5D system a preference index (utility) can be estimated that expresses the overall preference of the classified health status [41] [the Netherlands algorithm will be used to calculate the index]. This EQ-5D index measures objective quality of life and is a societal-based numerical quantification of the patients’ health status in a scale from-.594 to 1 (perfect health), 0 is (as bad as being dead). In addition, participants will be asked to rate the overall health related quality of life, by means of a visual analogue scale (EQ-5D VAS). The VAS is a 100-mm vertical line from worst (0) to optimal of health (100). The EQ-5D VAS represents the subjective quality of life.

Safety of baclofen will be assessed by the number and intensity of reported side effects, using weekly report of adverse effects on a checklist and standardized medical assessments. The side-effects checklist is based on published side effects of baclofen in the treatment of Multiple Sclerosis [42]. Side-effects are partly self-monitored (21 items) and partly observed (8 items) by a doctor or nurse practitioner. Every item is scored on a five-point Likert scale: never (0), seldom (1), sometimes (2), frequently (3) or always (4). Examples of items are vomiting, nausea and diarrhea. The checklist also contains 5 parameters measured by a doctor or nurse practitioner. Examples of parameters are body temperature and heart rate frequency.

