#### Additional measures

Addiction physicians will be asked to monitor withdrawal symptoms when tapering baclofen, using standard questions. These include a short check of the most reported withdrawal symptoms in the literature [43,44].

We will monitor the use of other substances over the last thirty days (number of days and quantity) using section 1 of the Measurement of Addicts for Triage and Evaluation (MATE) before and after detoxification and at follow up (3 months). The MATE is a Dutch instrument designed as an aid in the diagnosis of clinically relevant patient characteristics in substance use disorders according to the DSM-IV axes [45].

At 6 month period we will also report on the needed period of treatment with baclofen to maintain abstinence by monitoring relapse (Timeline Follow back) and craving assessment (DDQ, VAS) within the intervention group between those who used baclofen for 3 month only and those who choose to continue the treatment further.

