**Table 2 Tab2:** **Time measurements**

**Week**	**0**	**1**	**2**	**3**	**4**	**5**	**6**	**7**	**8**	**9**	**10**	**11**	**12**	**13**	**14**	**15**	**24**
Measurement	**T0**-baseline	**T1**											**T2**				**T3**
Mate section	xx												xx				x
EQ–5D	xx												xx				x
DASS	xx												xx				x
Mini-plus	xx												xx				x
Blood	xx						x						x				
Urine	xx						x						xx				x
Medical consult	2x	2x	2x	x	x			x			x		x	x	x		
Baclofen (mg)	0	15–30	45– 60											30–45	30–15	15–0	0
Baclofen Side effect	x	2x	2x	x	x			x			x		x				
VAS	xx	x	x	x	x			x			x		xx				x
DDQ	xx	x	x	x	x			x			x		xx				x
Baclofen withdrawal checklist														x	x	x	
Timeline follow back													xx				x

xx = baclofen group and control group TAU only.

x = baclofen group.

T0 = end of GHB detoxification.

T1 = start baclofen treatment.

T2 = follow-up TAU only and end of baclofen therapy.

T3 = follow-up baclofen group.

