### Statistical analyses

Descriptive analysis will be executed for all measurements and will include the mean, SD and frequencies of events with confidence intervals. Descriptive statistics will be used to compare the basic characteristics of the participants in the experimental group and the control groups. To assess any difference in relapse rates between the experimental group and the control groups (TAU group and matched historical group) at 3 month after detoxification Pearson Chi-squared test will be used for the dichotomous abstinence rates. ANOVA will be carried out on continuous variables, such as the total number of abstinent days, the maximum duration of continued abstinence, time before relapse (relapse defined as ≥ 3 times GHB use per day, for 2 subsequent days), and level of substance use over a period of 3 months. At 6 months period participants who continued baclofen will be compared to those who have stopped with baclofen (after 3 month) on relapse into GHB abuse or abstinence corrected for craving. The numbers of patients maintaining abstinence will be analysed with the intention-to-treat principles. The difference in craving will be analysed by MANCOVA at 3 months between groups (abstinent experimental versus abstinent TAU or relapsed TAU) with DDQ and VAS craving as dependent variables and corrected for craving levels immediately after detoxification. The change in craving in time during the baclofen treatment will be analysed via repeated measures MANOVA. By means of MANCOVA at 6 months after detoxification the difference in craving among participants who are still using baclofen and those who have discontinued baclofen will be analysed corrected for craving after 3 months. The effect of baclofen on the psychiatric symptoms levels (DASS, MINI) and also quality of life (EQ–5D) will be analyzed similarly as for craving at 3 and 6 months. The effects of the different TAU approaches as potential confounders will be tested in a sensitivity analyses (changing one-factor-at-a-time) in an linear regression including TAU per center as covariates.

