## Discussion

This study protocol presents the design of an open label clinical trial evaluating the efficacy of baclofen to prevent relapse, reduce craving and anxiety, and to assess the safety profile of baclofen in GHB dependent patients. To date, there are no reports on the potential of baclofen to prevent relapse in GHB dependent patients. We expect that baclofen will increase abstinence rates, reduce craving and will be well tolerated. In addition, baclofen may improve psychiatric symptoms such as anxiety and depression, as suggested in several clinical trials in alcohol-dependent individuals [29,30,46].

Several risks of baclofen use are taken into account in the current study. In patients with neuropsychiatric disorders, such as schizophrenia, severe depression, mania, Parkinson’s disease and cerebrovascular diseases, exacerbations of these conditions may occur, when the dose of baclofen is rapidly increased. It may lower the threshold for seizures in epileptic patients [42]. To limit these risks in the current trial, baclofen will be uploaded gradually, over a period of minimally 10 days. Moreover, patients previously diagnosed with any of the mentioned diseases will be excluded from the study.

Abrupt discontinuation of baclofen, when used for several months, can be associated with a withdrawal syndrome which resembles benzodiazepine and alcohol withdrawal. Several symptoms are reported such as hallucinations, fever, confusion, delirium, agitation, insomnia, and muscle stiffness and spasms [47]. Therefore, patients will be advised to taper down slowly when discontinuation is needed.

Intoxication with baclofen has been reported in doses above 100 mg [48]. This risk increases if patients combine baclofen with GHB. Intoxication is not expected when baclofen is administered at a low dose (<30 mg per gift), as applied in the current study. Patients will however, be informed repeatedly of this potential risk and the treatment will be discontinued immediately in case of relapse.

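### Scheduled safety collection in Table 2 ends before baclofen exposure ends, most clearly for patients who take the optional further 3 months

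*Protocol article*

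**What the plan says.** **Safety outcome.** Under Secondary outcome measures, baclofen safety is assessed by the number and intensity of side effects, "using weekly report of adverse effects on a checklist and standardized medical assessments". No end date is given. The section Statistical analyses analyses this outcome, and the Discussion and Implications for practice look ahead to conclusions about tolerability.

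**Exposure.** Table 1 runs baclofen through week 15, with the taper in weeks 13 to 15. Under Baclofen intervention there is an optional extension: "Patients who wished to continue the baclofen treatment will be offered an outpatient counselling and medication by their physician for another 3 months". Statistical analyses then compares craving at 6 months between "participants who are still using baclofen and those who have discontinued baclofen".

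**Schedule in Table 2.**
- The row "Baclofen Side effect" is filled at weeks 0, 1 (twice), 2 (twice), 3, 4, 7, 10 and 12.
- Blood is taken at weeks 0, 6 and 12.
- The row "Medical consult" is filled at weeks 0 to 4, 7, 10, 12, 13 and 14.
- The row "Baclofen withdrawal checklist" is filled at weeks 13, 14 and 15.
- Week 24 has outcome questionnaires, urine and the timeline follow-back. It has no side-effect or withdrawal checklist, and its baclofen entry is 0.

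**Withdrawal.** Additional measures says: "Addiction physicians will be asked to monitor withdrawal symptoms when tapering baclofen, using standard questions". No week is attached. The same section names relapse and craving as what will be compared between continuers and stoppers at 6 months. The Discussion gives the risk: "Abrupt discontinuation of baclofen, when used for several months, can be associated with a withdrawal syndrome".

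**The concern.** Safety is a stated outcome with its own analysis, so its collection should span the time patients take the drug. Table 2 ties collection to study weeks, and the side-effect rows stop at week 12. Patients who accept the extension are the longest exposed, and the plan analyses them as a group at 6 months. Yet for the extension period the schedule has no instrument that would record a side effect, and no withdrawal checklist for when they eventually come off.

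A side effect that arises or persists after week 12, or withdrawal when a continuer stops, could therefore go uncounted. A statement that baclofen was well tolerated would describe the first 12 weeks while appearing to describe the whole treatment. Missing reports would look the same as absent events, so the error would run towards safety.

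**Working it through.** The plan gives no figure for safety coverage, so the check is a count from Tables 1 and 2.

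**1. Side-effect checklist by phase (Table 2).**

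| Phase | Weeks | Weeks with side-effect checklist | Weeks with withdrawal checklist | Weeks with consult | Blood |
|---|---|---|---|---|---|
| Titration and maintenance | 1–12 | 7 of 12 (1, 2, 3, 4, 7, 10, 12) | 0 | 7 | 2 |
| Scheduled taper | 13–15 | 0 of 3 | 3 of 3 | 2 of 3 | 0 |
| After week 15 | 16–24 | 0 of 9 | 0 | 0 | 0 |

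Weeks 1 and 2 have two administrations each, so weeks 1–12 hold 9 administrations in 7 weeks. The empty weeks are 5, 6, 8, 9 and 11.

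**2. Dosing weeks without the side-effect checklist, against the promised weekly report.**
- Stop on schedule (15 dosing weeks, Table 1): 5 + 3 = 8 of 15 = 53%.
- Continue to week 24 (assumption: the further 3 months are 12 weeks counted from week 12): 5 + 12 = 17 of 24 = 71%.
- If the 3 months are instead counted from week 15: 5 + 3 + 12 = 20 of 27 = 74%.

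**3. Dosing weeks after the last side-effect checklist.** This isolates the early end of collection from the gaps before week 12.
- Stop on schedule: 3 of 15 = 20%.
- Continue to week 24: 12 of 24 = 50%.

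**4. Statements that do not agree.**
- Secondary outcome measures has a weekly report. Table 2 has 7 of the first 12 weeks and none later. Procedure and data collection ties side-effect monitoring to the regular medical check-ups and points to Table 2.
- Table 2 enters 0 for baclofen at week 24. Baclofen intervention supplies drug for 3 further months, and Statistical analyses expects some patients to be on it at 6 months.
- The text below Table 1 says stopping will be considered at relapse. The Discussion says treatment is stopped at once at relapse, and separately that patients are advised to taper slowly when discontinuation is needed.

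**5. What collection in continuers could show.** Their number is not given. Assuming that 25% to 75% of the 40 baclofen patients continue gives 10 to 30. With no event seen in n patients, the one-sided 95% upper limit for the event risk is 1 − 0.05^(1/n):
- n = 10: 26%
- n = 20: 14%
- n = 30: 9.5%

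These limits are wide but usable. With no collection, no limit can be set for the extension period.

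**The case against.** Several points on the other side are sound.

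- **The taper is not unmonitored.** A reader might infer from the end of the side-effect rows that the taper yields almost no safety data. Table 2 contradicts this: the withdrawal checklist falls in all three taper weeks and consults in two. Only the general side-effect checklist and blood are absent.
- **Withdrawal monitoring is already linked to tapering in the text.** The sentence in Additional measures has no week, so it may cover a continuer's later taper or a tapered early stop. It does not clearly cover an abrupt stop, and Table 2 still fixes the checklist at weeks 13 to 15.
- **The named risks do not all fall in the gap.** The Discussion puts one risk at rapid dose increase, which is the densely monitored titration phase. The risk of combining baclofen with GHB spans all exposure. The withdrawal sentence joins abrupt stopping with several months' use as one condition, so it does not single out a patient who stops in week 3 or a continuer who tapers under guidance.
- **Early stopping.** A reader might infer that patients who stop early are lost to safety follow-up. Nothing says their visits end, and assessments triggered by stopping may sit in the full protocol behind this article.
- **Continuers' taper.** It is tempting to say that it falls after the last study contact. The document does not say when or how they taper. Procedure and data collection also places the follow-up both at six months from the start of detoxification and at three months after baclofen ends.
- **The checklist is partly self-monitored.** A weekly self-report outside the listed contacts is possible, but the document does not describe one.

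The brevity of an article does not answer the main point, which rests on a printed schedule that conflicts with other printed statements.

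**Conclusion.** The point holds in a limited form. As printed, side-effect collection stops at week 12. Dosing runs to week 15 for patients on schedule and for a further 3 months for those who continue. The side-effect checklist is absent in 53% of dosing weeks for the former and about 71% for the latter (74% if the extension starts at week 15). After week 15, continuers have no scheduled side-effect checklist, consult, blood test or withdrawal checklist.

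The percentages rest on the column positions in Table 2 and on reading 3 months as 12 weeks. How many patients would have side effects or withdrawal unrecorded cannot be derived, because the plan gives neither a continuation rate nor a firm rule on stopping at relapse.

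Severity is moderate. Safety is a secondary outcome, the study describes itself as exploratory, and the primary outcome is unaffected. What is at risk is the tolerability conclusion for the longest-exposed patients.

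**What to change.** The change concerns data collection and reporting only.

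1. In Table 2, add the side-effect checklist to weeks 13 to 15, to continuers' physician contacts and to the existing week-24 visit.
2. Link the withdrawal checklist to each patient's actual dose reduction or stop, as the wording in Additional measures suggests, instead of to weeks 13 to 15 alone.
3. Report safety over actual time on baclofen. If collection is not extended, limit the safety conclusion explicitly to the first 12 weeks.
4. Reconcile the weekly report with Table 2, the week-24 baclofen entry with the optional extension and the 6-month analysis, and the two statements on stopping at relapse. Which dosing or stopping statement applies is for the sponsor to settle.

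The cost is a small amendment and a few short checklists at contacts that mostly already exist.

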**Table 1 Tab1:** **Baclofen dose in mg/week**

**Week**	**1**	**2**	**3**	**4**	**5**	**6**	**7**	**8**	**9**	**10**	**11**	**12**	**13**	**14**	**15**
Doses a day	15–30	45–60	45/60	45/60	45/60	45/60	45/60	45/60	45/60	45/60	45/60	45/60	30–45	15–30	15–0

Compliance will be assessed based on self-report, urine test for GHB, and empty pill counts. The physician will make use of the BRENDA method, a psychosocial program designed to enhance medication and treatment compliance [33,34]. In case of GHB use during baclofen treatment, participants are expected to contact the research physician. In case of relapse, immediate cessation of treatment will be considered to avoid intoxication hazards.

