## Methods and Design

### Study design

The design is of an open label non-randomized controlled clinical study in six addiction care facilities in the Netherlands. The study is part of the Dutch national GHB Monitor 2.0 and data collection will take place between May 2014 and December 2015. After successful detoxification of GHB, patients will receive either baclofen on top of treatment as usual (TAU + baclofen) or treatment as usual (TAU) only. Assignment is based on in- and exclusion criteria and on patient preference (informed consent).

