### Outcome and instruments

#### Primary outcome measures

The primary study outcome is the relapse rate, in other words the level of GHB use as indexed by the total number of abstinent days, the duration of continued abstinence after detoxification (CAD), time before relapse, and intensity of substance use over a period of 3 and 6 months (Timeline Follow-back Method).

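### The week-12 urine sample is scheduled in both concurrent groups but has no stated role in the primary abstinence comparison, which rests on unblinded patient recall

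*Protocol article*

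**What the plan says.** All references are to the protocol article.

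- **Primary outcome measures.** The outcome is the level of GHB use, indexed by abstinent days, continued abstinence, time before relapse and "intensity of substance use over a period of 3 and 6 months (Timeline Follow-back Method"). No biochemical confirmation is named.
- **Statistical analyses.** Dichotomous abstinence at 3 months is compared by Pearson chi-squared test and the continuous measures by ANOVA. Urine is not mentioned. Relapse is a pattern of use: "relapse defined as ≥ 3 times GHB use per day, for 2 subsequent days".
- **Baclofen intervention, after Table 1.** This is the only sentence that gives the urine GHB test a purpose: "Compliance will be assessed based on self-report, urine test for GHB, and empty pill counts".
- **Table 2.** Urine is marked xx at weeks 0 and 12 and x at weeks 6 and 24. The Timeline Follow-back is marked xx at week 12 and x at week 24. The footnote reads "xx = baclofen group and control group TAU only"; a single x means the baclofen group only.
- **Study design.** "The design is of an open label non-randomized controlled clinical study in six addiction care facilities in the Netherlands". Assignment depends partly on patient preference.
- **Consequence of relapse.** After Table 1: "In case of GHB use during baclofen treatment, participants are expected to contact the research physician", and "In case of relapse, immediate cessation of treatment will be considered to avoid intoxication hazards". The Discussion says instead that "the treatment will be discontinued immediately in case of relapse".

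**The concern.** A GHB assay shows whether GHB was taken. It says nothing about baclofen intake, so the information it carries concerns the outcome. The plan nevertheless places it under compliance and leaves the primary comparison on what patients recall and choose to report.

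That matters here because patients know their treatment and the two concurrent groups do not face the same consequence. A baclofen patient who discloses relapse may have the drug stopped; a TAU-only patient has no study drug to lose. If disclosure differs for that reason, the difference in abstinence rates mixes a drug effect with a reporting effect, and the test cannot separate them.

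**Working it through.** **1. Is there a usable sample?** At week 12, Table 2 marks both urine and the Timeline Follow-back xx. The sample and the self-report therefore come from the same week in both concurrent groups. The week-6 and week-24 samples are baclofen-only; using them in the group comparison would make detection unequal.

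**2. The plan's own figures (Sample size calculation).** The inputs are 70% abstinence with baclofen, 36% without, and multipliers 1.96 and 0.84.

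n = (1.96 + 0.84)² × (0.70 × 0.30 + 0.36 × 0.64) / 0.34² = 7.84 × 0.4404 / 0.1156 = 29.87, so 30 per group. With 25% drop-out, 30 / 0.75 = 40. Both stated figures reproduce. The point does not depend on them; they supply the 36% and the group sizes below.

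**3. What differential reporting could do.** Let u be the share of relapsed baclofen patients who conceal use. The documents give no value, so u is an assumption shown over a range. Take true abstinence of 36% in both groups and full reporting in TAU. Apparent baclofen abstinence is 0.36 + 0.64u. The last two columns give the exact probability that the two-sided Pearson chi-squared test rejects at 5%, summed over all binomial outcomes.

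| u (assumed) | Apparent baclofen abstinence | Spurious difference | Type I error, 30 per group | Type I error, 40 per group |
|---|---|---|---|---|
| 0 | 36.0% | 0 | 4.8% | 4.9% |
| 10% | 42.4% | 6.4 points | 7.8% | 9.2% |
| 20% | 48.8% | 12.8 points | 17% | 22% |
| 30% | 55.2% | 19.2 points | 33% | 43% |

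To produce the whole 34-point target difference, u would have to be 0.34 / 0.64 = 53%. If both groups concealed 20%, the error would stay near 5% (5.2% and 5.7%). The harm comes from a difference in reporting between groups, not from under-reporting as such.

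**4. What one sample could recover.** Background gives a plasma half-life of about 30–60 minutes, so a single sample can contradict only recent use. Let c be the share of concealers it catches, again assumed. Effective concealment is u(1 − c). At 40 per group:

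| u | No urine rule | c = 10% | c = 25% |
|---|---|---|---|
| 10% | 9% | 8% | 7% |
| 20% | 22% | 19% | 15% |
| 30% | 43% | 36% | 27% |

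The rule reduces the distortion but does not remove it.

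**The case against.** **The incentive is weakest when the outcome is recorded.** Table 2 labels week 12 the end of baclofen therapy, tapering follows in week 13, and research assistants assess both conditions identically. A patient then has little treatment left to lose. This stands in large part. The incentive is not absent, because patients who wish to continue are offered a further three months of baclofen.

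**The direction could be the opposite.** Baclofen patients have repeated consultations, an extra urine sample at week 6 and a request to report use. Closer contact could bring more relapse to light in that group. This stands. A reader might infer that the plan inflates abstinence in the baclofen group only. The documents do not support that: it needs an assumed level of concealment together with full honesty in TAU.

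**The error rates might be read as the benefit of the fix.** They are not. They size an assumed problem, and the second table shows that one sample recovers only part of it. Allocation by preference also means that the nominal error rate is not secured in any case, and the Discussion calls the study explorative.

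**The article may be condensing.** The full protocol could say how urine corroborates self-report, and Table 2 says only urine, so a GHB assay in the TAU group is an inference. Both cautions are fair. But the article is not silent: it assigns the test a role, and it names the outcome's source without urine.

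**Compliance may include abstinence.** The surrounding paragraph covers treatment compliance and GHB use as well as medication. That reading is reasonable, and taking the urine test off the compliance list would change no result, so the point does not ask for it.

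**Conclusion.** The point holds in a limited form. The article ties the primary abstinence comparison to unblinded recall, states no use for the urine GHB test other than compliance, and schedules a week-12 urine sample in both concurrent groups beside the Timeline Follow-back. Using that sample symmetrically is a better-founded method at almost no cost.

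Reporting may differ between groups because only one of them risks losing treatment. Whether it does, in which direction and by how much cannot be read from the documents. The figures of 8%, 17% and 33% (30 per group) and 9%, 22% and 43% (40 per group) rest wholly on assumed concealment of 10%, 20% and 30% in the baclofen group, none in TAU, and no true effect. With an assumed 10–25% of concealers caught, the figures at 40 per group fall only to about 7–8%, 15–19% and 27–36%.

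Separately, the statement after Table 1 that stopping after relapse is to be considered and the Discussion's unqualified statement that treatment is discontinued must be reconciled. This point takes no view on which is right and holds under either.

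**What to change.** - For baclofen versus concurrent TAU at 3 months, count a week-12 urine above a pre-set GHB cut-off as not abstinent in both groups, whatever the Timeline Follow-back says. The cut-off must allow for endogenous GHB, which Background describes.
- Show this result beside the self-report-only analysis, and report disagreement between self-report and urine by group.
- Apply the rule to dichotomous abstinence only. A single positive sample shows recent use, not the repeated use over two days that defines relapse, so it should not enter time to relapse.
- Keep the baclofen-only week-6 and week-24 urines out of the between-group outcome.
- Keep the self-report definition for the historical-control comparison, since no urine data are described for those patients.
- Confirm that the TAU week-12 urine is assayed for GHB.

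**Cost.** No new visits or samples; an added assay if the TAU urine is not already tested for GHB. Observed abstinence may be slightly lower. Baclofen abstinence will have one definition against concurrent TAU and another against historical controls, which showing the self-report analysis alongside makes plain. The check remains partial.
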